## Study Objectives

- (1) To measure the variation in clinical decisions among practicing VillageMD primary care providers in the assessment, recognition, and adjustment of treatment due to medication non-adherence and DDIs in patients with chronic cardiometabolic diseases.
- (2) To determine whether education about the Chronic Disease Management Test and provision of the Chronic Disease Management Test results (i.e., the intervention) improves the quality of care, as measured by evidence-based management decisions to recognize and manage medication non-adherence including DDIs and the chronic cardiometabolic conditions for which these medications are prescribed.
- (3) To model whether receiving the Chronic Disease Management Test results leads to higher-value and/or lower-cost care decisions, including avoidance of invasive diagnostic tests or interventions, reduction of unneeded specialist referrals, increased diagnosis and treatment of drug-drug interactions or care decisions that are expected to reduce overall costs (e.g., appropriate and safe medication prescription that will reduce risk of cardiometabolic morbidity and mortality).
- (4) To determine whether the Chronic Disease Management Test results differentially impact the quality of care for different patient types (use cases).
- (5) To determine whether the targeted implementation of the Chronic Disease Management Test at VillageMD clinics could serve as a proof of concept for the remaining VillageMD primary care providers nationwide.

|             |                                                                                                                                                |                      |
|-------------|------------------------------------------------------------------------------------------------------------------------------------------------|----------------------|
|             | Clinical Study Protocol                                                                                                                 |                      |
|             | Title: Measuring the Clinical Utility of Aegis's Chronic Disease Management Test among VillageMD Providers: A CPV® Randomized Controlled Trial |                      |
| Supersedes: | Document Number:                                                                                                                               |                      |

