## Outcome Measures

- Baseline levels of variation in the work-up, recognition, and management of medication non-adherence and/or DDI in patients with more than one cardiometabolic condition and associated polypharmacy among all participants.
- Pre- and post-difference in the overall and the work-up, recognition, and management quality scores between control providers using standard of care diagnostic tools and intervention providers with access to CDMT results.
- Differences in evidence-based decisions, particularly prescribing decisions, made by intervention providers and control providers, while controlling for provider and practice characteristics, between rounds 1 and 2.
- Distinguishing between medication non-adherence, DDI, and full compliance with suboptimal medication treatment (inadequate dosing vs. ineffective medication).
- Difference in expected cost of care between control and intervention providers (Cost will be calculated by measuring differential rates of medical interventions/levels of care selected by each arm, and multiplying by Medicare reimbursement rates for these interventions, and/or by modeling the incidence of expected complications and calculating associated costs per above).
- Difference in the above cost and clinical quality metrics by three different use case types.

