- 4) The intervention group, those who receive educational materials about the CDMT and CDMT results in their round 2 patients, will improve their quality of care and have less practice variation when caring for their CPV® patients with more than one chronic cardiometabolic condition and associated polypharmacy, as measured by management decisions to recognize and/or manage medication non-adherence, DDI, and associated co-morbidities.
- 5) The additional information from the CDMT will result in better distinction between medication non-adherence and DDI and lead to better overall care including reduction in over-use of invasive diagnostic work-up and treatment and a reduction in cost in a subset of patients. The associated cost savings, particularly for those patients will come from obviating high-cost workup, avoidance of unneeded subspecialty referrals, increased diagnosis and treatment of drug-drug interactions and/or reducing the frequency or number of medical interventions ordered.
- 6) Of the nine simulated cases that will focus on patients with multiple chronic cardiometabolic conditions and polypharmacy, there will be a subset of use cases where the CDMT demonstrates greatest utility for patients.
- 7) Providers with access to the education materials and CDMT will diagnose medication non-adherence and potentially harmful DDIs more often than control providers.

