## 2.1 Study Instruments

There are two data collection instruments: 1) the provider questionnaire; and 2) the CPV® simulated patient cases.

The online provider questionnaire consists of 10-15 questions to better understand provider demographics, training and practice environment. It will be administered once, upon enrollment into the study.

The CPV® cases will be designed to simulate typical patients with chronic cardiometabolic conditions and polypharmacy. In each case, providers will care for the simulated patient by indicating their preferred course of action to work- up, assess, and manage these patients. Providers will complete the cases in random order to cancel out any learning effects (which are known to be small), and only the intervention group will receive CDMT results at the appropriate point in each round 2 CPV® case whether they select it or not. All told, nine cases

|             |                                                                                                                                                |                       |
|-------------|------------------------------------------------------------------------------------------------------------------------------------------------|-----------------------|
|             | Clinical Study Protocol                                                                                                                 |                       |
|             | Title: Measuring the Clinical Utility of Aegis's Chronic Disease Management Test among VillageMD Providers: A CPV® Randomized Controlled Trial |                       |
| Supersedes: | Document Number:                                                                                                                               |                       |
|             | Effective Date:                                                                                                                                | Page: 16 of 25 |

will be developed, and any given provider will randomly be assigned to two rounds of three cases. Intervention will occur between the two rounds.

CPV® vignettes will be designed based on a 3 x 3 matrix of chronic cardiometabolic diseases and common drivers for non-adherence and potential drug-drug interactions.

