## 8. STATISTICAL ANALYSIS

### a. Study Hypotheses

1. Provider participants at baseline will not recognize that patients do not meet therapeutic goals due to medication non-adherence and show high levels of unwarranted variation in their work-up, recognition, and management of medication non-adherence in patients with more than one chronic cardiometabolic conditions and associated polypharmacy using in the CPV® patient simulations.
2. Providers will not recognize that patients do not meet therapeutic goals due to DDI and show high levels of unwarranted variation in their work-up, recognition, and management of medication non-adherence in patients with more than one chronic cardiometabolic conditions and associated polypharmacy using in the CPV® patient simulations.
3. The intervention group, those who receive educational materials about the CDMT and CDMT results in their round 2 patient, will improve their quality of care and have less practice variation when caring for their CPV® patients with more than one chronic cardiometabolic conditions and associated polypharmacy, as measured by management decisions to recognize and/or manage medication non-adherence, DDI, and associated co-morbidities.
4. The additional information from the CDMT will result in better distinction between medication non-adherence and DDI and lead to better overall care including reduction in over-use of invasive diagnostic work-up and treatment, and a reduction in cost in a subset of patients. The associated cost savings, particularly for those patients will come from obviating high-cost workup, avoidance of unneeded subspecialty referrals, increased diagnosis and treatment of drug-drug interactions and/or reducing the frequency or number of medical interventions ordered.
5. Of the nine simulated cases that will focus on patients with multiple chronic cardiometabolic conditions and polypharmacy, there will be a subset of use cases where the CDMT demonstrates greater utility.
6. Providers with access to the education materials and CDMT will diagnose

|             |                                                                                                                                                |                       |
|-------------|------------------------------------------------------------------------------------------------------------------------------------------------|-----------------------|

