##### *Longitudinal Data Analysis*

Primary Outcome Variables:

- Baseline variation in care among providers using standard of care tools, as measured by CPV® patient simulations
- In the intervention group, change in the overall and the diagnostic and treatment evidence-based quality scores and reductions in variation when caring for the CPV® simulated patient with the introduction of CDMT testing.

|             |                                                                                                                                                |                       |
|-------------|------------------------------------------------------------------------------------------------------------------------------------------------|-----------------------|
|             | Clinical Study Protocol                                                                                                                 |                       |
|             | Title: Measuring the Clinical Utility of Aegis’s Chronic Disease Management Test among VillageMD Providers: A CPV® Randomized Controlled Trial |                       |
| Supersedes: | Document Number:                                                                                                                               |                       |
|             | Effective Date:                                                                                                                                | Page: 22 of 25 |

- Changes in evidence-based management medication decisions (treatment) based on patient’s CDMT result.
- Distinguishing between medication non-adherence, DDI, and full compliance with suboptimal medication treatment (inadequate dosing vs. ineffective medication).
- Change in cost of chronic disease-related care. (This cost is modeled in part by measuring differential rates of work up/interventions/levels of care selected by each arm and multiplying by average Medicare reimbursement rates for these workups/interventions/ levels of care, and/or by modeling the incidence of expected complications and calculating associated costs per above).
- Difference in the above cost and clinical quality metrics and cost measures by three different use case types.

Secondary Outcome Variables:

- Calculation of the change in the expected cost and clinical quality metrics for each type simulated patient case (use case).

Main Explanatory Variable:

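### The use-case hypothesis is worded so that no result could refute it, and nothing printed ties the three use case types to the case matrix or tests for a difference between them

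*Protocol*

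**What the plan says.** The hypothesis appears twice. Item 6 of the synopsis list opens with "Of the nine simulated cases that will focus on patients with multiple chronic cardiometabolic conditions and polypharmacy" and continues "there will be a subset of use cases where the CDMT demonstrates greatest utility for patients". Section 8.a, item 5, has the weaker form "there will be a subset of use cases where the CDMT demonstrates greater utility". Neither gives a comparator, a threshold or a null.

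The objective behind it, Objective 4 in the synopsis and in Section 3, is put as an open question: "To determine whether the Chronic Disease Management Test results differentially impact the quality of care for different patient types (use cases").

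The outcome lists use a different count. The synopsis has "Difference in the above cost and clinical quality metrics by three different use case types". Section 3.1 repeats the item with small changes, and Section 8.b lists it among the primary outcome variables as "Difference in the above cost and clinical quality metrics and cost measures by three different use case types". Section 8.b then gives a closely related quantity, change in cost and quality by type of simulated case, as the secondary outcome.

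On structure, Section 2.1 states "CPV® vignettes will be designed based on a 3 x 3 matrix of chronic cardiometabolic diseases" crossed with drivers of non-adherence and interaction. The rows are COPD, HF/AF and DM/HTN; the columns are Variants A, B and C. Each provider is randomly assigned two rounds of three cases.

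In the Section 8.b model for CPV scores, CASE is defined as the position of the case in the provider's sequence. The interaction is CASE by INTERV. The binary-outcome model interacts TIME, a calendar period, with INTERV.

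**The concern.** A hypothesis has to be able to fail. This one is satisfied by any ranking of nine numbers, including when the intervention effect is identical in every case or absent from all of them. The change to greater in Section 8.a does not cure this, because it does not say greater than what.

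The unit is also left open. The matrix offers two sets of three types (variants or diseases) besides the nine single cells, so the grouping could be chosen after the results are seen.

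The stakes are practical. The Summary and Section 1 call finding the use cases where the test adds most value a key part of establishing clinical utility, and say that data on them are wanted for strategic, regulatory and educational ends. A use case that came top by chance could be put to those ends.

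**Working it through.** **Inputs from the protocol.** Synopsis, Sample Size: 166 recruited, 83 per arm, 75 per arm expected after 10% attrition. Check: 83 × 0.9 = 74.7, about 75, so the stated figure reproduces. Section 2.1: three cases per provider per round, drawn from nine. The Sample Size section gives no effect size, SD, alpha or power, so the results below are in SD units of a single CPV score.

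**Assumptions not in the protocol.** Cases spread evenly; scores independent with equal SD; two-sided 0.05 tests; the same true intervention effect in every case.

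**Scores per arm in round 2.**
- Per case: 75 × 3 / 9 = 25.
- Per type: 75 × 3 / 3 = 75.

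**Standard error of one arm difference, round 2 only: √(2/n).**
- Nine cases: √(2/25) = 0.283 SD.
- Three types: √(2/75) = 0.163 SD.

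**Difference-in-differences with independent rounds: √(4/n).**
- Nine cases: √(4/25) = 0.400 SD.
- Three types: √(4/75) = 0.231 SD.

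**Excess of the top estimate over the average.** Simulation of 400,000 trials with equal true effects gives an expected maximum of 1.486 SE for nine estimates and 0.846 SE for three.

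| | Nine cases | Three types |
|---|---|---|
| Excess, round 2 only | 1.486 × 0.283 = 0.42 SD | 0.846 × 0.163 = 0.14 SD |
| Excess, difference-in-differences | 1.486 × 0.400 = 0.59 SD | 0.846 × 0.231 = 0.20 SD |
| Chance that the round 2 excess is above 0.3 SD | 80% | 4% |
| Top versus rest, unadjusted, significant | 21% | 7.5% |
| Best versus worst, unadjusted, significant | 57% | 12% |
| Hypothesis met as worded | 100% | 100% |
| One test of equal effect, significant | 5.0% | 5.0% |

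The last two rows carry the point. With no true difference, the printed wording is confirmed every time, while a single test of equal effect is positive in 5.0% of trials under either grouping. The choice between nine and three alone changes the expected overstatement threefold (0.42 / 0.14 = 3).

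**Can the printed models answer Objective 4?** They contain CASE (order), INTERV, TIME and provider-practice variables. None identifies the disease row or the variant column, so no coefficient measures a difference in intervention effect between use cases.

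**The case against.** Several points on the other side are sound.

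- A reader might infer that the trial will always answer Objective 4 with yes. The documents do not support that. Objective 4 asks whether there is a differential impact and can be answered no; the fault lies in the hypothesis paired with it.
- A reader might infer that a chance winner will be reported. No section sets a rule to pick the highest estimate, and a statistical analysis plan, not available here, may supply a heterogeneity test. Only could be reported is supportable.
- A reader might take three types against nine cases as a contradiction. It is not: nine cases nest in three types. What is missing is the axis.
- The axis is signposted. Synopsis hypotheses 1 to 3 separate non-adherence, drug interaction and ineffective therapy, and one outcome concerns telling these apart. Both match Variants A, B and C, and no hypothesis is split by disease. This makes the variants the likely intention. It does not fix them: those hypotheses concern recognition and practice variation, not differences in effect, and Section 8.a leaves out the ineffective-therapy item.
- The 0.42 SD figure models a nine-cell ranking of round 2 scores that the protocol does not describe. The protocol plans difference-in-differences, and scores are clustered within provider; positive correlation would narrow the gaps between use cases. Under the three-type grouping named in the outcome lists, the figure is 0.14 SD.

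These points limit the consequence. They do not make the hypothesis refutable, and a test added in an analysis plan would leave the protocol's hypothesis met whatever that test showed.

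**Conclusion.** The concern holds in this form: the use-case hypothesis cannot be refuted as worded, the axis defining the three use case types is not stated although the item is listed as a primary outcome in Section 8.b, and the printed models contain no term that tests Objective 4. Followed as written, the protocol yields figures by use case with no test of whether they differ.

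The size depends on the grouping used. With equal true effects, the top estimate overstates the average by about 0.42 SD for nine cases and 0.14 SD for three types (round 2, independent scores, even allocation), or 0.59 and 0.20 SD under difference-in-differences with independent scores. These figures show what a ranking could produce; they do not forecast what the trial will report. The change should be made, because it alters what the trial can conclude about where the test is most useful.

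**What to change.** 1. Define use case once. Variants A, B and C appear intended; the sponsor could name the disease rows instead, provided that one axis is fixed before data are seen. Align the synopsis Outcome Measures and Study Hypothesis, Section 3.1, Section 8.a and both outcome lists in Section 8.b.
2. Replace synopsis item 6 and Section 8.a item 5 with a statement that can fail: *the intervention effect on the quality score differs between the three use case types*.
3. Add use case type to the model, with its interaction with intervention and round, and judge the hypothesis by one test of equal effect across the three types (3 − 1 = 2 degrees of freedom).
4. Claim that a use case is better only if that test is positive; otherwise report that no difference was shown. Label the other axis and the nine single cases as exploratory.

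The cost is revised wording and one added set of model terms. The sponsor gives up confirmatory naming of a single best case from the nine.

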## Data Analysis

A pre-post analysis will be conducted to compare practice patterns and performance of the intervention versus the control group (statistically a difference in difference fixed effects analysis). This analysis uses the CPV® scores as the outcome variable and includes basic bivariate analysis to determine group differences followed by a difference-in-difference, fixed effects multi-variate regression analysis, controlling for provider characteristics, to identify significant differences across the two groups.

|             |                                                                                                                                                |                       |
|-------------|------------------------------------------------------------------------------------------------------------------------------------------------|-----------------------|
|             | Clinical Study Protocol                                                                                                                 |                       |
|             | Title: Measuring the Clinical Utility of Aegis’s Chronic Disease Management Test among VillageMD Providers: A CPV® Randomized Controlled Trial |                       |
| Supersedes: | Document Number:                                                                                                                               |                       |
|             | Effective Date:                                                                                                                                | Page: 12 of 25 |

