## Study Design

The study is a prospective randomized cohort two-arm trial with six steps:

- 1) Enrollment: The study will enroll an estimated 166 practicing primary care providers, who practice at VillageMD clinics. An eligibility screener will be used to screen for eligibility (attached as Appendix A).
- 2) Provider survey: Once providers are enrolled in the study, they will be asked to complete an item questionnaire describing their practice, professional background and confidence in treating patients with cardiometabolic conditions.
- 3) Randomization: The 166 VillageMD providers will be randomized into two equally- sized arms: control group and intervention group.
- 4) CPVs® (First Round): Providers in both groups will complete three CPV® patient vignettes. Cases will be identical across the intervention and control arms. Cases are interactive and are presented on an online platform that is accessible via unique weblinks and any internet-connected computer.
- 5) Intervention education: For the intervention group, providers will receive educational materials describing the clinical validation and use cases of the Chronic Disease Management Test. The education materials are an orientation to the test, its use, the results directed to the participants that will adopt the CDMT (e.g., introduction slide deck, fact sheet, and/or case studies)
- 6) CPVs® (Second Round): All participating providers will then be asked to complete three additional CPV® patient simulations. The cases are again given to the doctors in a random order.

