### 3.1 Outcome Measures

- Baseline levels of variation in the work-up, recognition, and management of medication non-adherence and/or DDI in patients with more than one chronic cardiometabolic conditions and associated polypharmacy among all participants.
- Pre- and post-difference in the overall and the work-up, recognition and management quality scores between control providers using standard of care diagnostic tools and intervention providers with access to CDMT results.
- Differences in evidence-based decisions, particularly prescribing decisions, made by intervention providers and control providers, while controlling for provider and practice characteristics, between rounds 1 and 2.
- Distinguishing between medication non-adherence, DDI, and full compliance with suboptimal medication treatment (inadequate dosing vs. ineffective medication).
- Difference in expected cost of care between control and intervention providers (Cost will be calculated by measuring differential rates of medical interventions/levels of care selected by each arm, and multiplying by Medicare reimbursement rates for these interventions, and/or by modeling the incidence of expected complications and calculating associated costs per above).
- Difference in the above cost and clinical quality metrics and cost measures by three different use case types.

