- Intervention status (exposure to intervention)

We will control for all potential confounders, including:

- Age
- Gender
- Years in practice
- Practice location
- Type of location (urban/suburban vs. rural)
- Weekly hours in clinical practice
- Number of providers in practice
- Avg. type of coverage of patients (Medicare, Medicaid, commercial, etc.)
- Participation in care quality incentive programs
- Percentage of patients that have chronic cardiometabolic disease

We will model CPV® scores as a continuous outcome variable in a multiple linear regression model, which controls for all potential confounders listed above.

Our regression model is as follows, where CPV® is the score for each provider and INTERV indicates intervention group and CASE indicates the order in which the provider took the case (first, second, third, fourth).

|             |                                                                                                                                                |                       |
|-------------|------------------------------------------------------------------------------------------------------------------------------------------------|-----------------------|
|             | Clinical Study Protocol                                                                                                                 |                       |
|             | Title: Measuring the Clinical Utility of Aegis’s Chronic Disease Management Test among VillageMD Providers: A CPV® Randomized Controlled Trial |                       |
| Supersedes: | Document Number:                                                                                                                               |                       |
|             | Effective Date:                                                                                                                                | Page: 23 of 25 |

$$Y_{it} = \text{CPV}^{\circledR} \text{ score of provider } i, \text{ at time } t$$

$$Y_{it} \sim \text{Normal}(\mu_{ijt}, \sigma^2)$$

$$\mu_{ijt} = \beta_0 + \beta_1 \text{CASE} + \beta_2 \text{INTERV} + \beta_3 \text{CASE} \times \text{INTERV} + \text{provider-practice variables}$$

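### The difference-in-difference analysis of the continuous CPV score uses the round 1 score only by subtraction, so the arm comparison is less precise than the collected data allow

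*Protocol*

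**What the plan says.** Providers are "randomized into two equally- sized arms: control group and intervention group" (Synopsis, Study Design, step 3). Before any intervention, "Providers in both groups will complete three CPV® patient vignettes" (step 4), and a second set of three follows. Section 2.1 adds that nine cases will be written and "any given provider will randomly be assigned to two rounds of three cases".

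The Synopsis (Data Analysis) names the estimator: "statistically a difference in difference fixed effects analysis", starting with bivariate comparisons and then a "difference-in-difference, fixed effects multi-variate regression analysis, controlling for provider characteristics, to identify significant differences across the two groups". Section 3.1 frames the outcome in the same way: "Pre- and post-difference in the overall and the work-up, recognition and management quality scores between control providers" and intervention providers.

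Section 8.b (Longitudinal Data Analysis) gives the model: "We will model CPV® scores as a continuous outcome variable in a multiple linear regression model", "which controls for all potential confounders listed above". That list covers age, gender, years in practice, location, hours, practice size, payer mix and similar descriptors. The equation has CASE, INTERV, their product and provider-practice variables. Neither the list nor the equation contains the provider's round 1 score.

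Under Section 4.c, a provider who does not finish three cases in each round is withdrawn, replaced and left out of the analysis. Every analysed provider therefore has both round means.

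**The concern.** Each round mean rests on three vignettes, and the two rounds use different cases. The round 1 mean is therefore a noisy measure of a provider's usual performance. Difference-in-difference subtracts it with a coefficient of exactly one, so its noise goes in full into the arm contrast. A regression of the round 2 mean on arm and round 1 mean (ANCOVA) lets the data set that coefficient and discounts the noise.

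The listed provider characteristics do not recover the loss. In balanced two-round data, characteristics that do not change between rounds, entered as main effects, leave the arm-by-round contrast unchanged. If provider fixed effects are meant, they absorb those characteristics entirely.

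At stake is the standard error of the comparison of CPV quality scores, in a trial that expects 75 providers per arm.

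**Working it through.** **Inputs from the protocol.** 1:1 randomisation; three cases per provider per round; 83 recruited and 75 expected per arm after 10% attrition (Synopsis, Sample Size). The stated size reproduces: 83 × 0.9 = 74.7, and 75/0.9 = 83.3. No effect size, SD, alpha or power is stated.

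**Assumed inputs.** ρ, the between-provider share of case-level variance: 0.1 to 0.5. Where power is shown, two-sided alpha 0.05 and a notional 80% for the difference-in-difference analysis; neither figure is the protocol's.

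**Step 1: what the named estimator is.** With two rounds and complete data, the difference-in-difference estimate equals the between-arm difference in mean change.

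**Step 2: variances.** Let σ² be the variance of a provider's round mean and r the correlation between the two round means. Per provider:

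- difference-in-difference: 2σ²(1 − r)
- round 1-adjusted: σ²(1 − r²)
- ratio, adjusted to difference-in-difference: (1 − r²)/[2(1 − r)] = (1 + r)/2, below 1 whenever r < 1.

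If the round SDs are σ₁ and σ₂, the difference-in-difference variance exceeds the adjusted one by (σ₁ − rσ₂)², which cannot be negative. The direction therefore does not depend on equal variances, but the exact ratios do.

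**Step 3: r from ρ.** With three cases per round, r = 3ρ/(1 + 2ρ). At ρ = 0.1 this is 0.3/1.2 = 0.25.

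| ρ (assumed) | r | Variance ratio (1+r)/2 | SE smaller by | Per arm to match 75 | Power if difference-in-difference has 80% |
|---|---|---|---|---|---|
| 0.1 | 0.25 | 0.63 | 21% | 47 | 94% |
| 0.2 | 0.43 | 0.71 | 15% | 54 | 91% |
| 0.3 | 0.56 | 0.78 | 12% | 59 | 89% |
| 0.5 | 0.75 | 0.88 | 6% | 66 | 85% |

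The SE reduction is 1 − √ratio, and the matching number per arm is 75 × ratio. At r = 0.9 the ratio is 0.95, the matching number 72 per arm, and the power 82%.

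**Step 4: simulation check.** A case-level simulation with 75 per arm and 4,000 runs gave ratios of 0.63, 0.73, 0.81 and 0.89 for the four rows, close to the formula.

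**Step 5: a reference point.** Ignoring round 1 altogether has variance σ². Difference-in-difference is worse than that when 2(1 − r) > 1, that is, when r < 0.5.

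**Step 6: the price of switching.** Adjustment uses one degree of freedom of about 147 (150 − 3). Suppose exclusion and replacement of non-completers leave the arms differing by d in stable provider ability. Difference-in-difference removes d. The adjusted analysis removes rd and leaves (1 − r)d: 75%, 44% and 25% of d at ρ = 0.1, 0.3 and 0.5.

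**The case against.** Difference-in-difference is a valid analysis here. It is unbiased under randomisation and fits both the pre/post wording of the outcomes and the aim of looking for the changes seen in QURE 3. This stands as a reason to keep reporting it, but not as a reason to make the less precise estimator the main one. The outcome wording is no obstacle: regressing the change score on arm and round 1 score gives the same arm coefficient as regressing the round 2 score on them.

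The Section 8.b equation is not the Synopsis analysis. It has no provider effect, and CASE is the order of the case, so the ratio (1+r)/2 describes the Synopsis estimator and not that interaction term. This also stands, but the equation omits the round 1 score too, so it does not supply the missing adjustment.

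The strongest objection concerns Section 4.c. Exclusion and replacement after randomisation mean that the analysed arms are not strictly the randomised arms, and only the intervention arm has extra material between rounds. A reader might infer that baseline adjustment is free of cost. It is not quite: Step 6 shows what it would leave behind. Nothing in the protocol says whether d differs from zero. The sensitivity analysis is there for this case.

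A reader might also extend the gain to the use-case contrasts and the binary outcomes. The protocol does not support that. Section 2.1 does not guarantee each provider a round 1 case of the same type as in round 2, and the use-case contrasts were not calculated. In the logistic model, adding a prognostic covariate changes the odds ratio being estimated, so the argument that both analyses target the same effect does not carry over.

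**Conclusion.** The point holds for the continuous CPV quality score as a matter of precision. Under intact randomisation both analyses estimate the same effect, so the planned one should not be read as biased.

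Its variance is larger than necessary by a factor of 2/(1+r) under equal round variances. The adjusted variance is about 0.63 to 0.88 of the difference-in-difference variance for an assumed between-provider share of 0.1 to 0.5, and 0.95 at r = 0.9. A low to moderate r is plausible with three cases per round, but the protocol gives no value. Hypothesis 4 of the Synopsis expects less variation in the intervention group, so the exact ratios may shift while the direction does not.

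A reader might take the power column as the trial's own loss of power. It is not: the protocol states no power, SD, effect size or alpha, so that loss cannot be computed. The change is worth making, but its size is uncertain.

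**What to change.** In the Synopsis (Data Analysis) and Section 8.b, state that the main comparison of the continuous CPV score is the between-arm difference in round 2 score, adjusted for the provider's mean round 1 score. Keep the difference-in-difference estimate as a named sensitivity analysis, with the exclusion and replacement rule in Section 4.c given as the reason. Leave the binary models and the use-case contrasts outside this change.

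The cost is a sentence in each place and a round 1 term in the Section 8.b linear model. No new data and no further providers are needed. The statistical cost is one degree of freedom and weaker protection against any imbalance caused by non-completion, which the retained sensitivity analysis would help to show.
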